#### Sample size and power

The cRCT will focus on 25 OTIP hospitals. We aim to interview on average 30 hospital staff per hospital and 50 mother-newborn pairs. In total, the sample for the cRCT will be 750 staff, and 1250 mother/newborns per data collection round.

We calculate minimum detectable effects (MDEs) using the following formula [13]:1$$MDE\left(\frac{\left(t_{\alpha/2}+t_\beta\right)^2\sigma^2(mp\left(1-R_c^2\right)+\left(1-p\right)\left(1-R_p^2\right)}n\right)^\frac12$$

$$\:\alpha\:$$ denotes the significance level, $$\:\beta\:$$ power, $$\:\rho\:$$ unconditional ICC, $$\:t$$ is the critical values of the t-distribution, $$\:\sigma\:$$ is the standard deviation of the outcome,$$\:\:n$$ is midwives/mothers per arm, $$\:m$$ is midwives/mothers per cluster, $$\:{R}_{c}^{2}$$ is proportion of cluster level variance component explained by covariates and $$\:{R}_{p}^{2}$$ is the individual equivalent. One can interpret the effect of $$\:{R}_{c}^{2}$$ and $$\:{R}_{p}^{2}$$ as altering the “variance inflation factor” of the power calculation– when they equal zero the formula reduces to the standard cRCT one, applicable in our case.

To calculate the minimum detectable effects (MDEs), we assume a significance level ($$\:\alpha\:$$) of 0.05 and power ($$\:\beta\:$$) of 0.8 using two-sided tests.

To estimate intra-cluster correlations (ICCs) for the outcomes we measure, we reference the 2005 WHO Global Survey on Maternal and Perinatal Health [14], which presents ICCs that were obtained from 97,095 pregnancies and 98,072 births taking place in a representative sample of 120 hospitals in eight Latin American countries:Process variables: ICCs range from a minimum of 0.0003 to a maximum of 0.563, with a median of 0.067.Maternal outcome variables: Median ICC of 0.011 (interquartile range 0.007–0.037).Neonatal outcomes: Median ICC of 0.054 (interquartile range 0.013–0.075).

For hospital staff outcomes, we use data collected by colleagues on midwives in Nigeria to get an idea of hospital staff outcomes. The data provide indices that capture emotional exhaustion, accomplishment, and depersonalization (based on the Maslach Burnout Inventory).Hospital staff outcomes: ICCs of 0.07 for emotional exhaustion, 0.12 for accomplishment, and 0.07 for depersonalization.

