As we will collect baseline data, we will be able to gain precision, allowing us to reduce ICC. We therefore assume ICCs of between 0.01 and 0.3 for process outcomes, 0.01 for maternal and neonatal outcomes, and no more than 0.1 for hospital staff outcomes.

Table 1 provides MDEs for all outcome groups. We note that since we assume that all outcomes considered will be continuous normally distributed variables standardized to have mean zero and standard deviation of one relative to the control group, the estimated MDE’s do not vary by outcomes, but rather by sample size we have for each outcome group.

**Table 1 Tab1:** Minimum detectable effects (standard deviations)

Outcome	MDE for different ICCs		
	0.01	0.1	0.3
Process (1,250)	0.196	0.390	0.637
Mother/child (1,250)	0.196	0.390	
Midwife level (750)	0.236	0.410	

For process variables, our RCT sample yields MDEs between 0.196 and 0.64 for two-sided tests. For maternal and newborn outcomes, the MDE is between 0.196 and 0.39. For hospital staff outcomes, the expected MDE is between 0.36 and 0.41.

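### The lower end of the hospital-staff MDE range is 0.236 in Table 1 but 0.36 in the text, and the upper end of 0.41 depends on an unquantified baseline gain

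*Protocol article*

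**What the plan says.** All of this is in the Protocol article, section Sample size and power.

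- **Cited staff ICCs.** From burnout indices collected on midwives in Nigeria, the article reports "ICCs of 0.07 for emotional exhaustion, 0.12 for accomplishment, and 0.07 for depersonalization".
- **Assumed staff ICC.** The article expects baseline data to add precision and so lower the ICC. On that ground it assumes a staff ICC of at most 0.1.
- **Formula.** The MDE formula has two R-squared terms for covariates, at cluster and individual level. The article says that with both at zero it becomes the standard cluster-trial formula, and that this is the version that applies here.
- **Table 1.** The columns are ICC 0.01, 0.1 and 0.3. The row beginning "Midwife level (750" holds 0.236 under 0.01 and 0.410 under 0.1.
- **Summary sentence.** "For hospital staff outcomes, the expected MDE is between 0.36 and 0.41". No ICC is attached to either end.

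For process outcomes and for mother and newborn outcomes, the same paragraph repeats the two ends of the table row. Only the staff sentence departs from its row.

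**The concern.** Two statements of the same quantity, a few lines apart, disagree at the lower end by a factor of about 1.5 (0.36/0.236). The text does not say which ICC its figure uses, so a reader cannot tell whether the sentence rests on a different ICC or has lost a digit from 0.236.

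The staff outcomes are secondary, but the article uses them to explain how the programme works. If the mechanism result is null, readers will look up what the trial could have detected. Anyone who takes 0.24 SD from Table 1 would read a null result as stronger evidence against a staff mechanism than the cited ICCs allow.

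A second and smaller issue is the upper end. The cap of 0.1 excludes one of the three cited ICCs, and the reason given for lowering it never enters the calculation.

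**Working it through.** **Inputs, all from Sample size and power**

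- Two-sided level and power: "of 0.05 and power" and "of 0.8 using two-sided tests".
- Outcomes are "standardized to have mean zero and standard deviation of one relative to the control group", so SD = 1.
- "We aim to interview on average 30 hospital staff per hospital and 50 mother-newborn pairs", so m = 30 for staff and 50 for mothers.
- "the sample for the cRCT will be 750 staff, and 1250 mother/newborns per data collection round", so with near-equal arms n is about 375 staff and 625 mothers per arm.
- Both R-squared terms are zero.

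**Formula**

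MDE = M × √[ 2 (mρ + 1 − ρ) / n ], where M is the sum of the two quantiles and ρ is the ICC. The formula as it appears in the text I read has no factor 2. Without it, normal quantiles give staff values of 0.164 and 0.286, which do not match the table, so the table was evidently computed with it.

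The article does not state M. Normal quantiles give 1.960 + 0.842 = 2.80, and t quantiles on 23 df give about 2.93. M = 2.84 reproduces every cell of Table 1. It is inferred from the table and is not a documented value.

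**Step 1: reproduce Table 1 with M = 2.84**

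| Row | ICC | mρ + 1 − ρ | MDE | Table 1 |
|---|---|---|---|---|
| Mothers (n = 625, m = 50) | 0.01 | 1.49 | 0.196 | 0.196 |
| Mothers | 0.10 | 5.90 | 0.390 | 0.390 |
| Mothers | 0.30 | 15.70 | 0.637 | 0.637 |
| Staff (n = 375, m = 30) | 0.01 | 1.29 | 0.236 | 0.236 |
| Staff | 0.10 | 3.90 | 0.410 | 0.410 |

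**Step 2: staff MDE at the cited ICCs**

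- ICC 0.07: 2.84 × √(2 × 3.03 / 375) = 0.361
- ICC 0.12: 2.84 × √(2 × 4.48 / 375) = 0.439

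The 0.36 in the text therefore matches ICC 0.07. With normal quantiles and 12 against 13 hospitals, solving for the ICC that gives 0.36 returns 0.072.

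**Step 3: sensitivity to the quantiles (12 against 13 hospitals)**

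| ICC | Normal | M = 2.84 (equal arms) | t, 23 df |
|---|---|---|---|
| 0.01 | 0.233 | 0.236 | 0.243 |
| 0.07 | 0.356 | 0.361 | 0.372 |
| 0.10 | 0.404 | 0.410 | 0.422 |
| 0.12 | 0.433 | 0.439 | 0.453 |

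**Step 4: size of the differences**

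- 0.236 against 0.361: 1 − 0.236/0.361 = 35% lower.
- 0.410 against 0.439: 1 − 0.410/0.439 = 7% lower.

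**Step 5: baseline gain needed to justify the lower figures**

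The article's formula allows the gain to enter through the cluster-level R-squared, with the individual-level term left at zero.

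- From ICC 0.07 to an MDE of 0.236: 30 × 0.07 × (1 − R²) + 0.93 = 1.29, so 1 − R² = 0.36/2.1 = 0.171 and R² is about 0.83.
- From ICC 0.12 to an MDE of 0.410: 30 × 0.12 × (1 − R²) + 0.88 = 3.90, so 1 − R² = 3.02/3.6 = 0.839 and R² is about 0.16.

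Neither value is stated in the article.

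**The case against.** The strongest reply is that nothing has been miscalculated. Table 1 is a grid with labelled columns, and 0.236 is correct under its heading of 0.01. The sentence after it already prints the more cautious 0.36, which covers two of the three cited ICCs. This stands: a reader might infer that Table 1 contains an arithmetic error, and Step 1 shows that it does not.

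The second reply concerns the upper end. A reader might infer that 0.41 is simply wrong and that 0.44 must replace it. The article does not support that. The cap of 0.1 is a stated assumption with a stated reason. The reason is plausible too: the same midwives are to be interviewed throughout (Sample size, sampling, and recruitment), and ANCOVA is allowed where baseline values exist (Statistical methods). A cluster-level R-squared of about 0.16 is enough. If both R-squared terms are equal, 1 − 3.90/4.48 = 0.13 suffices, a baseline-to-follow-up correlation of about 0.36. What remains is that the gain is not quantified, while the same section says the formula with zero R-squared applies and the table reproduces at zero.

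Third, the cited ICCs come from burnout scales in another country and are offered only as a guide, whereas the trial's staff outcomes are knowledge, autonomy, empowerment and motivation. Clinical knowledge is also to be collected online from 1,338 midwives, about 53.5 per hospital. At full response and M = 2.84, the MDE there is about 0.34 at ICC 0.07 and 0.42 at ICC 0.12. So 0.36 to 0.44 describes the 750 in-person interviews and should not be carried over to the online knowledge survey. This limits the reach of the point but gives no support for 0.01.

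None of these replies explains why the sentence departs from its table row without naming an ICC.

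**Conclusion.** The point holds as a minor inconsistency in a stated power figure. The staff range has two different lower ends, 0.236 and 0.36, which correspond to ICCs of 0.01 and about 0.07. The upper end of 0.41 (ICC 0.10) is common to both.

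No cited staff ICC is close to 0.01, and the R-squared of about 0.83 needed to get from 0.07 to 0.236 appears nowhere, so 0.236 should not be presented as an expected staff MDE. At the upper end, the MDE for the cited ICC of 0.12 without a baseline gain is about 0.44 (0.43 to 0.45). The article's 0.41 can be defended if a modest gain is assumed and stated.

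The figures assume 30 staff in each of 25 hospitals, SD 1, zero R-squared unless noted, and a multiplier inferred from Table 1. Whether 0.36 is an unlabelled ICC 0.07 value or a misprint of 0.236 cannot be settled from the article; either way the two places must be reconciled. Only secondary outcomes are affected. A reader might go further and infer that the trial's design or primary power is undermined. The article gives no ground for that: the 25 hospitals are all those eligible in the final phase, and the mother-level rows agree with their text.

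**What to change.** 1. Add columns for ICC 0.07 and 0.12 to Table 1 and fill the midwife row with about 0.36 and 0.44. Do not put the 0.07 value under the existing 0.01 heading.
2. Drop the midwife entry at ICC 0.01, or mark it as illustrative.
3. In the summary sentence, name the ICC behind each end of the staff range.
4. Then choose one of two wordings. Either give the range as 0.36 to 0.44 (ICC 0.07 to 0.12, no baseline gain), or keep 0.36 to 0.41 and state the R-squared assumed from the midwife baseline, about 0.16 at cluster level, in place of the general remark that baseline data reduce the ICC.

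The cost is two table columns and one or two sentences. Sample size, design and conduct do not change.

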#### Participant timeline

Hospitals were randomized into early and late treated in July 2024. Pre-intervention implementation data was collected in September 2024. The first set of OTIP trainings took place in October 2024, the second will be conducted in February 2025. Data collection for primary outcome analysis will be conducted in January 2025. Mothers for the impact analysis will be recruited from early January 2025 and data collection is expected to take one month. The participant timeline is presented in Fig. 3.

**Fig. 3 Fig3:**
[figure not shown]
Participant Timeline

#### Sample size, sampling, and recruitment

The total targeted sample size for the cRCT will be in-person interviews with 750 staff, and 1,250 patients (mothers) per data collection round. In addition to the in-person survey we will administer online surveys to all the midwives on permanent contracts working in each hospital to collect data on clinical knowledge (1,338 midwives in total).

The patients target sample sizes proportional to each hospital’s delivery caseload in August-October 2023. This results in a minimum sample size of 35 and a maximum sample size of 65 per hospital. The inclusion criteria will be those who delivered in the hospital within the last two months, primarily from labor wards, postnatal wards, and postnatal care clinics. This eligibility criteria implies that in each survey round, we will interview a new cross section of 1,250 mothers. For mothers 18 years or younger, interviews will only be conducted if a guardian is present and provides consent in addition to the mother doing so herself. Mothers will only be approached for interview if not in distress due to, for example, having lost their child during labor. We will cross-check with hospital staff whether mothers can be approached or not.

The sample of midwives for these interviews will consist of the 10 midwives nominated by management or their peers to become champions (of whom 7 will ultimately be selected for training) and a random sample of 20 other midwives with permanent contracts in the maternity department, resulting in a total midwife sample of 750 midwives. We will not interview any students or staff on temporary contracts in the hospital. We aim to interview the same set of midwives throughout the study.

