#### Eligibility criteria

The cRCT will focus on the 25 hospitals that will receive the OTIP program during the final phase of the national roll-out, which has been planned in three phases (see Supplementary Materials S.3 for names of study sites). The first two phases of the roll-out were completed by April 2024. The third and final phase of the rollout was started in September 2024, covering all eligible hospitals, 25 in total, in Greater Accra, Central and Western regions.

Within each study hospital, target participants will be mothers that delivered in the hospital within the last two months prior to data collection. They will not be selected if they are facing post-birth complications, or if they are below the age of 18 and a guardian is not present. Data from mothers recruited in January 2024 will be the basis for the impact evaluation. We in addition collect information from mothers who were present prior to intervention implementation. These will however not be exposed to the OTIP intervention.

We will further conduct interviews with individuals who will perform the intervention, e.g. midwives. We will interview those that are selected to be OTIP champions, and a random sample of non-champion midwives on permanent contracts in the maternity department, including those in charge of wards and clinics. We will also administer online surveys to all the midwives on permanent contracts working in each hospital to collect data on clinical knowledge (1,338 midwives in total).

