#### Assignment of interventions

Randomization was conducted using Stata version 16 by researchers at the IFS. The randomization determined whether a hospital would receive the intervention earlier or later. The decision whether a patient is assigned to the intervention or control group therefore depends on the timing of inclusion. By end February 2025 all hospitals will have received the intervention and hence by then every patient will be included in treatment. There is no blinding. Inclusion in the study for assessment of intervention effectiveness will be completed by the end of January 2025.

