#### Statistical methods

For our process variables, we will estimate the intent-to-treat effect of the program. Our design is a cluster randomized controlled trial stratified by region.

We estimate the impact of OTIP on process and maternal and neonatal outcomes by estimating the following specification for the outcome *Y* of mother or baby *i* in hospital *j* in region *r* at time *t*:2$$Y_{ij}=\beta\;OTIP_j+\delta\;X_{ij}+Y_r+\epsilon_{ij}$$.

Where $$\:OTI{P}_{j}$$ indicates if a hospital is allocated to receive OTIP early, $$\:{\varvec{X}}_{ij}$$ is a vector of controls for hospital characteristics selected by machine learning methods, and $$\:{\gamma\:}_{r}$$ are region fixed effects, as we stratified our randomisation by region to ensure balance in earlier and later treated hospitals in each region.

To increase statistical power, we will leverage the panel nature of our data and use baseline values of the outcomes in our analysis. For observations with values collected at baseline and follow-up, we can use an ANCOVA design. For observations without baseline values, we can use a difference-in-differences specification, exploiting variation across early- and later-treated hospitals, before and after the introduction of OTIP in early-treated.

To investigate mechanisms behind the observed impacts, we will use the same design with hospital staff outcomes to understand whether any impacts are driven by changes in staff outcomes due to OTIIP, such as midwives’ clinical knowledge and attitudes.

Moreover, for outcomes with low serial correlation, we will follow [15] and pool the multiple follow-up measurements to average out noise and increase power.

Due to the small number of clusters (25), we will present a wild-bootstrap p-value that is robust to small numbers of clusters [16]. We will additionally adjust for multiple hypothesis testing by family of outcome. Lastly, we will test for balance using baseline data for outcomes for hospital, midwives and patients’ characteristics. We will also test if attrition is uncorrelated to treatment allocation, and in case of non-random attrition on treatment status, we will estimate our main specification using inverse probability weighting.

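### Hospital staff, unblinded and after early-arm training, are consulted on which mothers may be approached; withholding that shifts differently between arms could bias the process comparison, and the planned checks would not reveal it

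*Protocol article*

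**What the plan says.** The order of events is in the Participant timeline section of the protocol article. "Hospitals were randomized into early and late treated in July 2024"; early hospitals were trained in October 2024; and "Mothers for the impact analysis will be recruited from early January 2025". Under Assignment of interventions the article states: "There is no blinding".

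Two rules that call for judgement limit who is interviewed. Eligibility criteria says of mothers: "They will not be selected if they are facing post-birth complications". Sample size, sampling, and recruitment adds: "Mothers will only be approached for interview if not in distress due to, for example, having lost their child during labor". The next sentence is: "We will cross-check with hospital staff whether mothers can be approached or not".

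Outcomes lists two sets of primary outcomes. One is the process of care, such as how soon a woman was first assessed and whether she was assessed when she arrived. Data collection and management says that the cluster trial relies mainly on interviews with mothers and midwives.

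For mothers, "in each survey round, we will interview a new cross section of 1,250 mothers"; only midwives are meant to be re-interviewed. Statistical methods plans a balance test on baseline data, an ANCOVA or difference-in-differences analysis depending on whether baseline values exist, and this: "We will also test if attrition is uncorrelated to treatment allocation", with inverse probability weighting if attrition depends on allocation.

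**The concern.** Recruiting individuals after clusters have been allocated is a familiar weak point of unblinded cluster trials. Randomisation balances the hospitals. It does not balance the interviewed women if entry to the sample can respond to allocation.

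Here the people consulted on entry work for the hospital whose care is being measured. Bad faith is not needed for a problem to arise. OTIP trains staff to classify women by risk, and that could change whom they regard as unfit to be approached. If the women withheld had a different experience of care from those interviewed, and withholding shifts in one arm only, the arms will differ on process outcomes without any true effect, or a true effect will be masked.

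It would also go unseen. If each hospital fills its target number, withheld women are replaced and the count of interviews gives no sign.

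**Working it through.** **1. Can the planned checks reach it?**

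- *Attrition test and weighting.* These need a person who was enrolled and then lost. Mothers are a fresh cross-section each round, so a woman who was never approached has no record to test or weight. The check can work for the midwife panel only.
- *Balance test.* It uses baseline data from September 2024. Selection in January 2025 lies outside it.
- *Difference-in-differences.* Write v for the share withheld and g for the gap in SD between retained and withheld women. With g constant, the remaining bias is [(v1,post − v1,pre) − (v0,post − v0,pre)] × g. This is zero if gatekeeping in each arm is stable over time. It is not zero if withholding changes in one arm after training.

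**2. Yardstick: the plan's own minimum detectable effects (Table 1).** Inputs: 25 hospitals split 12 and 13, 50 mothers each, so 600 and 650 mothers; two-sided alpha 0.05, power 0.80, SD 1.

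MDE = (1.960 + 0.842) × √[DE × (1/600 + 1/650)], with DE = 1 + 49 × ICC.

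| ICC | DE | SE | MDE, 12 v 13 | MDE, 12 v 12 | Stated |
|---|---|---|---|---|---|
| 0.01 | 1.49 | 0.0691 | 0.194 | 0.197 | 0.196 |
| 0.1 | 5.9 | 0.1375 | 0.385 | 0.393 | 0.390 |
| 0.3 | 15.7 | 0.2243 | 0.628 | 0.641 | 0.637 |

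The stated figures reproduce to within 1.5% and are used unchanged below.

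**3. Bias from differential withholding.** If R is the mean of retained women, the mean of all eligible women is (1 − v)R + v(R − g) = R − vg. The observed arm mean is therefore shifted by vg, and with a common g the bias in the difference between arms is (v1 − v0) × g. The values of v and g are assumptions; the documents give none.

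| Withheld, one arm v other | g (SD) | Bias (SD) | % of 0.196 | % of 0.390 | % of 0.637 |
|---|---|---|---|---|---|
| 10% v 5% | 0.5 | 0.025 | 13% | 6% | 4% |
| 10% v 5% | 1.0 | 0.05 | 26% | 13% | 8% |
| 15% v 5% | 1.0 | 0.10 | 51% | 26% | 16% |

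For a hospital with 50 interviews, 5%, 10% and 15% withheld correspond to about 3, 6 and 9 women (50/0.95 − 50 = 2.6; 50/0.90 − 50 = 5.6; 50/0.85 − 50 = 8.8).

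**4. Check with a different model.** Let withholding depend on a latent normal score with correlation r to the outcome. The shift in an arm is then r × φ(z_v)/(1 − v). With r = 0.5 the bias is 0.043 SD at 10% v 5% and 0.083 SD at 15% v 5%, the same order as above.

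**5. Effect on the error rate.** With no true effect, the chance of a significant result is 1 − Φ(1.96 − b/SE) + Φ(−1.96 − b/SE). For b = 0.10 SD this is 30% at ICC 0.01 and 11% at ICC 0.1. For b = 0.05 SD it is 11% and 6.5%. The nominal rate is 5%.

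**The case against.** The strongest reply is that the sentence describes an ethical safeguard. It follows directly on the clause about distressed mothers and speaks of a cross-check. Enumerators come from an outside company in daily contact with the research team. A reader might infer that staff choose the sample; the text does not say so. What stands is that a negative answer works as a veto, on an open-ended ground.

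A reader might also infer that those consulted are the maternity staff being assessed, or the Champions charged with promoting the protocol. The article says only that they are hospital staff. The link that the documents support is to the hospital, not to particular individuals.

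Nor is it right that the plan has no defence. Difference-in-differences suits repeated cross-sections, the September 2024 round came before training, and one recruitment procedure is described for every round. Stable gatekeeping therefore cancels. Only a change that differs between arms survives, which narrows the concern but does not remove it.

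The article is a condensed account. That it mentions no random draw of mothers and no screening log does not show that neither exists, and nothing here rests on that silence. The point rests on two things that are stated: a consultation step after allocation, and checks that cannot reach it.

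Finally, the direction is open. If OTIP prevents bad outcomes, fewer early-arm women would be distressed and withheld, which could work against OTIP. Late-arm staff could equally shield women who were poorly served. The ground for withholding also overlaps with the separate exclusion of women with complications or a loss.

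**Conclusion.** The concern holds as a risk to the process comparison. The documents do not show that bias occurred, and they do not support a claim that it favours the early arm.

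Under the assumed shares and gaps the bias is 0.025 to 0.10 SD. The 51% figure should not be read alone: it pairs the largest assumed contrast with the smallest stated detectable effect (ICC 0.01). The article assumes ICCs up to 0.3 for process outcomes, and there the same 0.10 SD is 16%. The bias matters most for process outcomes with little clustering, where the trial claims its best precision.

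The calculation assumes the same gap g in both arms and that withholding is related to the care received. If the gap differs, equal withholding shares could still bias the comparison.

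On dates, Eligibility criteria places recruitment of the analysed mothers in January 2024 and Participant timeline in January 2025. These must be reconciled; only the second fits the dates of randomisation and training, and it is the one used here.

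**What to change.** 1. Have enumerators select eligible mothers by a fixed rule, random or consecutive, before consulting staff: from the delivery list where one is available, otherwise from ward and clinic attendance. The article shows that delivery caseloads are known by hospital, but it does not say that individual lists are accessible, hence the alternative.
2. Keep the staff distress check in full, but as a veto on a woman already selected.
3. Record anonymous counts by hospital: selected, vetoed (by reason category), not found, refused, interviewed. Counts are enough. Individual data on women who were never asked would conflict with the article's rule that consent comes before any data collection.
4. Compare these counts by arm, and compare the January 2025 mothers between arms on characteristics fixed before delivery.
5. Add a bounds or sensitivity analysis for differential withholding. The counts give v1 and v0, so the analysis can report how large g would have to be to overturn the result.
6. State that the attrition test and weighting apply to the midwife panel.

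The cost is slightly slower recruitment, a short screening log and one additional analysis. If fieldwork is already complete, the comparison of January 2025 mothers and the sensitivity analysis can still be done, together with a report of any screening records that were kept.
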